## Blinding

The study will involve three separate teams—trained teachers, project staff, and the research team. Trained teachers will be responsible for administering the interventions; the teachers will be blinded to the K10 results. Project staff will be responsible for ensuring participant compliance, collecting the filled K10 questionnaires as photos via WhatsApp, and printing the photos and storing them until data analysis; project staff will be blinded to data analysis. The research team will be responsible for study design, participant recruitment, obtaining written informed consent, data analysis and reporting; the research team will be blinded to participant group allocation.

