Does continued practice influence the effect of the interventions in people experiencing homelessness	The decrease from baselines to delayed post-intervention and long-term follow-up Kessler psychological distress scale scores will be significantly larger in all intervention groups in participants who continue the practices learned during the intervention compared to that in participants who do not continue the practices learned during the intervention	54 participants each in the Bhagavad Gita group, Kuchipudi dance group, Both Bhagavad Gita and Kuchipudi dance group, and Control group for 80% power and 5% alpha	Participants in each group will be subdivided based on whether or not they continued practice during each follow-up. Repeated measures analysis of variance will be conducted on the subgroups	If our hypothesis holds true, it would suggest that sustained practice contributes to greater psychological well-being. Conversely, if there are no significant differences in the decrease of the Kessler psychological distress scale scores between participants who continue and those who do not continue the practices, it would indicate that continued practice does not play a significant role in the effectiveness of the interventions

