### Outcomes and measures

The primary outcome is psychological distress measured by the Kessler scale of psychological distress (K10) in this study. The K10 is a 10-item questionnaire that measures psychological distress based on questions about anxiety and depressive symptoms. It has previously been used in research conducted with PEH [17, 18]. At the immediate post-intervention, delayed post-intervention, and long-term follow-up measurements, apart from the K10, the participants will be asked if they have continued practicing the techniques learned during the intervention (Kuchipudi group: continued practice of the choreography, Gita group: continued self-reflection on the teachings of the Bhagavad Gita, Both group: continued practice of the choreography and continued self-reflection on the teachings of the Bhagavad Gita, and control group: none). The study flowchart is presented in Fig 2.

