### Data collection and management procedures

During each scheduled measurement session, the participants will be asked to take the questionnaire they were provided with in the sealed envelopes given to them at the time of enrolment that is pre-filled with the date of the appropriate measurement session. They will then be asked to hold the questionnaire sheet with the date visible to the camera and trained research support staff will check that each participant is holding the correct questionnaire. They will then walk the participants through how to fill in the questionnaire. Once they confirm that the questionnaires have been filled, they will walk the participants through how to take a photograph of the sheet and send the photo to the staff member via WhatsApp. Once the staff member receives legible photographs of the filled questionnaires from all participants, the meetings will be ended. The project staff will then save the photographs into as portable document format files on a secure computer situated in the research office of our organization and print out the same for our records. Our organization’s policy is to store both soft and hard copies of all research material—the soft copies are stored for a period of 2 years and the hard copies are stored for a period of 10 years. The research team will have unrestricted access to the final dataset.

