#### Adjustment and interpretation based on contamination checks

If contamination is detected, we will take the following steps to adjust or interpret the study results:

Quantification of Contamination: We will quantify the extent of contamination by calculating the percentage of participants who have been exposed to details about interventions other than their own.Statistical Adjustment: We will use statistical techniques to adjust for contamination. For instance, we might include contamination status as a covariate in our regression models to control for its potential impact on the study outcomes.Sensitivity Analyses: We will conduct sensitivity analyses to assess the robustness of our findings. This will involve comparing the results of the main analysis with those obtained after excluding contaminated participants or adjusting for contamination.Interpretation of Results: In the discussion section, we will interpret our findings in light of the contamination checks. We will acknowledge the presence of contamination, describe its potential impact on the study outcomes, and discuss how our adjustments have accounted for it.

This SAP will be reviewed and updated as necessary throughout the study to ensure the robustness and integrity of the analyses and findings.

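### The research team's allocation blind does not hold at the analysis stage, because the continued-practice item it must analyse exposes at least the control arm

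*Protocol article*

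**What the plan says.** The Blinding section describes three teams and what each is kept from knowing.

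- Teachers: "the teachers will be blinded to the K10 results".
- Project staff: "project staff will be blinded to data analysis".
- Research team: "the research team will be blinded to participant group allocation". Its duties are listed in the same sentence: "The research team will be responsible for study design, participant recruitment, obtaining written informed consent, data analysis and reporting".

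Only the third is a blind to allocation, and it carries no time limit or exception. Participants learn their arm from the envelope (Participants section).

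Outcomes and measures adds a question on continued practice to the K10 at all three post-intervention sessions and spells out its content by arm. For one arm it reads "Gita group: continued self-reflection on the teachings of the Bhagavad Gita". For the Kuchipudi arm it is practice of the choreography, for the Both arm it is the two together, and for controls there is nothing.

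Table 1 (Introduction) then uses the answer. Rows 1, 2 and 4 enter it as a covariate. For row 3, "Participants in each group will be subdivided based on whether or not they continued practice during each follow-up".

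On access, Data collection and management procedures states: "The research team will have unrestricted access to the final dataset". The article mentions no masked arm code, recoded practice variable or separate unblinded analyst.

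**The concern.** The team that is declared blind has to work with a variable whose content, or absence, depends on the arm. The primary between-group contrasts (Primary analysis section) are each intervention against control. Knowing which group is the control is therefore enough to see the direction of all three.

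This matters because several decisions that can move the result are left to be taken with data in hand:

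- Complete-case analysis or multiple imputation depends on a post-hoc power result (Plan for handling missing data and protocol deviations). The later Handling of missing data section favours imputation, particularly above 5% missing.
- Alternative models or transformations may be used if assumptions fail (Sensitivity analyses).
- The SAP stays open: "This SAP will be reviewed and updated as necessary throughout the study". Meanwhile interim results are analysed and published from Weeks 13–19, before the 1-year measurement in Week 56 (Timeline).

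The organisation running the trial itself chose to introduce the Gita teaching (Introduction), so a real analyst blind has value here. A final report that described the analysis as blinded would be inaccurate if nothing changed.

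**Working it through.** The plan gives no figure for blinding, so there is nothing to reproduce. The check sets the sections against each other and counts who could be identified.

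**Inputs**
- 256 recruited, 64 per arm in four arms, 16% dropout expected (Sample size calculation).
- Practice item at every post-baseline session, defined by arm, none for controls (Outcomes and measures).
- Item used in all four rows of Table 1.
- Research team analyses (Blinding) and has unrestricted dataset access (Data collection and management procedures).

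**Case A: item stored as a generic yes/no, with no entry for controls**
- Identified: 64 / 256 = 25%, all of them controls.
- The other 256 − 64 = 192 can only be guessed, with a one-in-three chance each: 192 / 3 = 64 correct.
- Expected correct assignments: (64 + 64) / 256 = 50%, against 25% by chance.
- The count is all 64 because the team needs some arm label to fit the model, and the label whose members never have a practice entry is the control arm. That also places any control who dropped out early.

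**Case B: item stored in its arm-specific form**
- The four contents (choreography, reflection, both, none) map one-to-one to the four arms.
- Everyone with at least one post-baseline form is identified from their own answers. If the whole dropout comes before the first form, that is 256 × (1 − 0.16) = 215.04, about 215 people. If dropout comes later, the number is larger, up to 256.

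**A second route**
The section on contamination checks plans to calculate the percentage of participants exposed to interventions other than their own and to use contamination status as a covariate. Deriving that status needs each person's arm, so this item also bears on the blind.

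**Where the blind does hold**
The research team recruits and takes consent. At that point the envelope is sealed and the participant is told not to disclose its contents to the team (Participants). Nothing in the practice item affects that stage.

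**The case against.** The strongest case on the other side has five parts.

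1. Outcomes and measures can be read as one generic question, with the brackets only explaining what it means in each arm. The form is not shown, and row 3 of Table 1 uses the answer as a yes/no. This stands. A reader might infer that every participant's arm is revealed with certainty, but the documents do not establish that. It is the upper case (Case B), and Case A is the lower one. Case A still exposes the control arm.

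2. A reader might also infer that the blind fails altogether. It does not, because the sealed envelopes can protect recruitment and consent.

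3. Splitting each group by practice can be done under masked labels, access to the final dataset carries no date, and the article does not say who enters the data. A condensed article may also leave masking details to a fuller document. This is fair, and the absence of those details is not the point. The point is an unqualified blind stated beside an analysis variable that undoes it.

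4. The analyst's freedom is easily overstated. Bonferroni is fixed for the primary pairwise comparisons. The choice among three corrections is offered alongside the subgroup analyses. Outlier exclusion is a with-and-without sensitivity analysis. None of these should be counted as open choices on the primary result. The missing-data method, alternative models or transformations, and SAP updates remain.

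5. K10 is self-reported by people who know their arm, so masking the analyst does nothing for reporting bias. This is correct, and it limits what the blind can achieve.

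**Conclusion.** The point holds for data handling and analysis only. The Blinding section claims something the plan, as written, does not deliver there. The size runs from the 64 controls (25% of 256) if practice is stored as a generic yes/no with no entry for controls, to everyone with a post-baseline form (about 215 of 256 under the earliest possible dropout) if it is stored by arm. Both figures assume that the practice data reach the analysts alongside the K10 data, which is what Table 1 and the access statement imply. The lower figure also assumes that controls' entries are left empty.

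Even the lower case matters, because the primary contrasts are all against control. The consequence is exposure of the remaining analytic choices to knowledge of the direction of effect. It is not a bias in the K10 responses themselves, and the documents give no basis for putting a number on any shift in the result. The plan should be changed on this point, but the defect does not invalidate the design.

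**What to change.** 1. Freeze the SAP before any outcome data are released. Because interim results will be published well before Week 56, the frozen text should also cover the 1-year analysis.
2. Have someone outside the research team prepare the first release. The independent statistician who already generates the allocation (Participants) is a natural choice. Release K10 and baseline data under masked arm codes, without the practice and contamination items.
3. Under those codes, take and sign off the missing-data, model and transformation decisions, and run the primary GEE of the Primary analysis section without the continued-practice covariate. That section lists no covariates. Table 1 names practice beside GEE and ANCOVA without making clear whether it enters the GEE, so the text should say that it does not enter the primary model. Practice is measured after randomisation and is not defined for controls.
4. Then release the allocation key and the practice and contamination data for the practice-adjusted Table 1 analyses and the contamination analyses.
5. Reword the Blinding section to say that the research team is blind at recruitment and until that sign-off. If the staged release is not adopted, the claim should be limited to recruitment and consent.

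The cost is one extra data release, duties for the statistician beyond those the article now describes, and practice-adjusted models that become a second-stage analysis. No change to recruitment, visits or sample size is needed.

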### Plan for handling missing data and protocol deviations

In case we are unable to recruit the required number of participants for the study from only Chennai and Dhanbad during the envisaged recruitment period, we will open the recruitment to the remaining locations that Samanjasa Foundation operates in, i.e., Hyderabad and Bhubaneshwar, India, and extend the recruitment period by another 4 weeks. Consequently, the timelines for the baseline measurements, interventions, and all post-intervention measurements will be delayed by 4 weeks. To minimize missing data, the participants will be given clear written instructions in their mother tongue and the project staff will regularly follow-up with the participants to ensure that they will not drop out of the study. Before the scheduled meetings, the participants will receive text messages and a phone call reminder from the project staff. Depending on post-hoc power analysis results, missing data will be handled either by complete case analysis or multiple imputation. Protocol deviations may result from technology failure and failure of the participants to comply with the interventions. The clear written instructions to the participants in their mother tongue and regular follow-up by project staff will help facilitate participant compliance. In case of technology failure, the project staff will video call the participants through WhatsApp, as the participants are more familiar with it than with Zoom. To prevent technology failure due to running out of data, all participants will receive an unlimited data recharge with one month validity one day before the scheduled baseline, delayed post-intervention, and long-term follow-up measurements. This can also serve as an incentive to the participants to attend the scheduled measurement sessions and help minimize missing data. In case of technology failure due to other reasons, the participants will be offered catch-up sessions before the next scheduled session.

### Statistical analysis plan (SAP)

This SAP outlines the procedures for data cleaning, handling missing data, conducting primary and subgroup analyses, and performing sensitivity analyses to ensure the robustness of the findings.

### Data cleaning

Data Entry and Validation: All data will be entered into a secure electronic database. Double data entry will be performed to ensure accuracy. Discrepancies will be resolved by consulting the original data source.Consistency Checks: Logical checks will be conducted to identify any inconsistencies (e.g., age values outside the expected range). Outliers will be flagged and verified with the original data.Descriptive Summaries: Baseline characteristics of participants will be summarized using means and standard deviations for continuous variables and frequencies and percentages for categorical variables.

### Handling of missing data

Identification: Missing data will be identified and categorized (e.g., missing completely at random, missing at random, or not missing at random).Imputation: Multiple imputation methods will be used to handle missing data, particularly if the proportion of missing data exceeds 5%. Sensitivity analyses will be conducted to compare the results from imputed and non-imputed datasets.Documentation: The extent and nature of missing data will be documented and reported.

### Primary analysis

GEE Framework: The primary outcome, psychological distress as measured by the K10 scale, will be analyzed using the GEE framework. Robust standard errors will be used to account for correlated data due to repeated measures. An exchangeable correlation structure will be assumed.Primary Comparisons: Comparisons will be made between each intervention group (Gita, Kuchipudi, and Both) and the control group. Within each intervention group, comparisons over time (pre-intervention, immediate post-intervention, 40 days post-intervention, and 1-year post-intervention) will be performed.Pairwise Post-Hoc Comparisons: Pairwise post-hoc comparisons will be conducted following significant GEE results to identify specific group differences. The Bonferroni correction will be applied to control for the risk of type I error in these multiple comparisons.

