Is learning the Bhagavad Gita better at reducing psychological distress than engaging in a hobby in people experiencing homelessness	The decrease from baselines to immediately post-intervention, delayed post-intervention, and long-term follow-up Kessler psychological distress scale scores will be significantly larger in the Bhagavad Gita group than in the Kuchipudi dance group	54 participants each in the Bhagavad Gita group, Kuchipudi dance group, Both Bhagavad Gita and Kuchipudi dance group, and Control group for 80% power and 5% alpha	Intergroup differences will be analysed by the generalised estimating equation and analysis of covariance with continued practice and religion as covariates. Subgroup analyses will be conducted by stratifying the participants in each group by age, religion (Hindu, Non-Hindu), educational attainment, and employment. Post-hoc power analyses will be conducted to verify the robustness and reliability of the subgroup analyses	If our hypothesis holds true, it would suggest that learning the Bhagavad Gita is more effective at reducing psychological distress than engaging in a hobby for people experiencing homelessness. By conducting subgroup analyses, we will further investigate if the effectiveness of the intervention varies based on age, religion, educational attainment, and employment

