Does learning the Bhagavad Gita provide any added benefit to people experiencing homelessness who are engaging in a recreational activity in terms of reducing their psychological distress	The decrease from baselines to immediately post-intervention, delayed post-intervention, and long-term follow-up Kessler psychological distress scale scores will be significantly larger in the Both group than the Bhagavad Gita and Kuchipudi dance groups	54 participants each in the Bhagavad Gita group, Kuchipudi dance group, Both Bhagavad Gita and Kuchipudi dance group, and Control group for 80% power and 5% alpha	Intergroup differences will be analysed by the generalised estimating equation and analysis of covariance with continued practice and religion as covariates. Subgroup analyses will be conducted by stratifying the participants in each group by age, religion (Hindu, Non-Hindu), educational attainment, and employment. Post-hoc power analyses will be conducted to verify the robustness and reliability of the subgroup analyses	If the reduction in the Kessler psychological distress scale scores is highest in the Both group, it would suggest that learning the Bhagavad Gita combined with engaging in a recreational activity may offer additional benefits in reducing psychological distress among homeless persons compared to learning the Bhagavad Gita group or engaging in a recreational activity alone. This finding would indicate that the combination of the intervention has a more substantial effect on decreasing distress levels

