### Participants

Persons meeting the criteria for the definition of a houseless person—someone who does not live in a building or "census houses," but rather in the open or seeks shelter in public places such as railway stations, under flyovers, places of worship, etc.—according to the 2011 Census of India, and residing in Chennai or Dhanbad, India during and after the Unlock 2.0 phase of the COVID-19 pandemic in India, aged >18 years will be recruited. Persons with a formal diagnosis of anxiety, depression, and any other mental illness will be excluded from the study and provided access to evidence-based treatments. All PEH availing the services of Samanjasa Foundation in Chennai and Dhanbad will be approached to participate in the study; the study information will be disseminated through the case workers. During earlier studies we found that this strategy ensures nearly 90% response rate; therefore, we are expecting a similar enrolment rate in this study as well. The participants will be divided into four groups—the Bhagavad Gita (Gita), Kuchipudi dance (Kuchipudi), both Bhagavad Gita and Kuchipudi dance (Both), and control groups—in a 1:1:1:1 ratio. The participant identification number, group assignment, four copies of a questionnaire with pre-filled participant ID and follow-up date, meeting schedule, and Zoom meeting link will be sealed in a small envelope and the envelopes will be placed in a fishbowl and shuffled. The participant ID will be generated in a random order by an independent statistician using a pseudo-random number generator script in Python 3.9.13. Group assignment will be generated in sequence by the independent statistician; the participant ID generated first will be associated with the Gita group, the second with the Kuchipudi group, the third with the Both group, the fourth with the Control group, the fifth with the Gita group, and so on. The project staff will fill and seal the envelopes with the respective contents. Once a participant provides written informed consent to participate in the study, they will be asked to pull an envelope from the fishbowl and not reveal its contents to the research team. They will also be instructed not to read the questionnaires until the sessions scheduled for the purpose of filling them out. To monitor and minimize the risk of contamination, especially given the potential for participants within the same community to communicate, the project staff will send weekly text messages to the participants regarding not sharing details about the intervention with anyone, including their family members. Additionally, the project staff will randomly contact three participants from each group via a phone call every two months and ask them if they had heard anything about the interventions in the other study groups. Furthermore, during community events and interactions, case workers will be asked to assess the level of knowledge regarding the intervention among the PEH. The participant journey is illustrated in Fig 1.

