### Statistical methods

#### Data analysis

All results will be reported in accordance with the CONSORT guidelines to ensure comprehensive and transparent reporting of the trial’s outcomes. Descriptive summaries of baseline characteristics will be presented to provide an overview of the study population. The comparisons will be between each intervention group and the control group, as well as within each intervention group over time. The repeated measures data will be analysed using the generalised estimating equation (GEE) framework. For the analysis of the primary outcome using the GEE framework, robust standard errors will be used to account for correlated data. Pairwise post-hoc comparisons will be conducted to identify specific group differences. To control for the risk of type I error in these multiple comparisons, the Bonferroni correction will be applied. Subgroup analysis will be conducted using analysis of covariance (ANCOVA) or non-parametric ANCOVA [19] depending on the normality of the data; this may include stratification by age, educational attainment, religion, and employment status. Multiple comparisons will also be addressed using appropriate statistical corrections. These may include the Bonferroni correction, Holm’s adjustment, or the Benjamini-Hochberg procedure, depending on the specific comparisons and the number of tests conducted. The data analysis will be conducted using Python 3.9.13. Statistical significance will be set at a two-tailed p < 0.05.

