#### Sample size calculation

The required sample size for GEE was calculated using the formula,

$$n=[(Z\alpha /2+Z\beta {)}^{2}*V\_eff]/(\Delta^{2}*\rho^{2}),$$

where n is the required sample size per group; Zα/2 is the critical value of the standard normal distribution for a two-tailed test with a significance level of α; Zβ is the critical value of the standard normal distribution for a specified power (1-β) of the test; V_eff is the effective sample size, which accounts for the correlation between the repeated measures within individuals; Δ is the minimum clinically significant difference; r is the number of repeated measures; and ρ is the correlation between the repeated measures.

Assuming a conservative value of 0.5 for ρ based on previous literature [20, 21], and for an α of 5%, 1-β of 80%, r of 4, and Δ of 7 [22, 23], we can calculate the effective sample size as follows:

$$\begin{array}{l} V\_eff=n/(1+(r‐1)*\rho )\\ \;=55/(1+(4‐1)*0.5)\\ \;=22.5 \end{array}$$

Therefore, n can be calculated as follows:

$$\begin{array}{l} n=[(1.96+0.84{)}^{2}*22.5]/(7^{2}*0.5^{2})\\ \;=53.3 \end{array}$$

Thus, at least 54 participants per group must be enrolled to have 80% power to detect a minimum clinically significant difference of 7 points between the groups using GEE, with a significance level of 5%. As there are four groups in the study, a total of 216 participants (54 per group) must be enrolled. Based on our previous experience, a dropout rate of 16% was expected; to account for this, we aim to recruit a total of 256 participants, with 64 participants per group.

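### The between-group K10 analyses name neither baseline K10 as a covariate nor a common baseline mean, so precision available from data already collected is not secured

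*Protocol article*

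**What the plan says.** Under Primary analysis, "The primary outcome, psychological distress as measured by the K10 scale, will be analyzed using the GEE framework", with robust standard errors and an exchangeable correlation structure. The pre-intervention score is one of the four time points analysed there, and the Abstract and the Interventions section list the same four measurements. The mean model is not written out.

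Table 1 is more specific. For question 2 (Gita against Kuchipudi) and question 4 (Both against either single intervention), between-group differences are to be analysed by GEE and "analysis of covariance with continued practice and religion as covariates". The hypothesis for question 2 is that "The decrease from baselines to immediately post-intervention, delayed post-intervention, and long-term follow-up Kessler psychological distress scale scores will be significantly larger" in the Gita group, and question 4 is worded in the same way. So the stated contrast is a difference in change from baseline.

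The Sample size calculation section supplies the correlation: "Assuming a conservative value of 0.5 for ρ based on previous literature". No section names baseline K10 as a covariate or says that the groups have a common mean at baseline.

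**The concern.** The plan does choose covariates for the between-group models, and the pre-intervention score on the outcome scale is not among them. In a randomised trial that score is usually the covariate that explains most of the outcome variance. Using it only to form a change score, or only as one more repeated outcome with free group means, is valid but gives a wider interval than the same data allow.

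The contrasts that can least afford this are the active-against-active ones in questions 2 and 4, where differences may be smaller than against no intervention. Four groups give 4 × 3 / 2 = 6 possible pairwise comparisons, and the pairwise comparisons are to be Bonferroni-corrected.

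**Working it through.** **Inputs from the article.** Correlation between repeated K10 scores ρ = 0.5, r = 4 measurements and 54 per group (Sample size calculation); exchangeable structure (Primary analysis); equal allocation (Participants). No K10 standard deviation is stated, so variances are in units of σ², per participant, for a contrast between two groups of equal size.

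**The plan's own figure.** The article gives no precision figure for baseline adjustment. The nearest stated figure is 54 per group, and it does not reproduce: 55/(1 + 3 × 0.5) = 22.0, not 22.5, and (1.96 + 0.84)² × 22.5/(7² × 0.5²) = 7.84 × 22.5/12.25 = 14.4, not 53.3. That is a separate matter. Here 54 serves only as the planned group size, and the ratios below do not depend on it.

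**Variance at one follow-up visit.**
- Follow-up score only: 1
- Change from baseline, group means free at baseline: 2(1−ρ)
- Adjusted for baseline, or common baseline mean: 1−ρ²

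| ρ | Follow-up only | Change | Adjusted | Reduction v change | Reduction v follow-up only |
|---|---|---|---|---|---|
| 0.3 | 1.00 | 1.40 | 0.91 | 35% | 9% |
| 0.5 | 1.00 | 1.00 | 0.75 | 25% | 25% |
| 0.7 | 1.00 | 0.60 | 0.51 | 15% | 49% |

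At ρ = 0.5 the standard-error ratio is √0.75 = 0.866, so intervals are about 13% narrower. Then 54/0.75 = 72: 54 per group with adjustment carry the information of 72 without. Conversely, 54 × 0.75 = 40.5, so about 41 adjusted match 54 unadjusted.

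**Check in the four-time-point model.** Generalised least squares with exchangeable ρ = 0.5 and two groups of n gives a change-contrast variance of 2.0 σ²/n when the group-by-time means are unconstrained, and 1.5 σ²/n when the groups share a baseline mean. The ratio is again 0.75.

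**Average of the three follow-ups, ρ = 0.5.** Unadjusted: (1 + 2ρ)/3 = 0.667, and the change-score version is the same because 1−2ρ = 0. Adjusted: 0.667 − ρ² = 0.417. The reduction is 1 − 0.417/0.667 = 37.5%.

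**The case against.** A reader might infer that the K10 analysis ignores baseline and certainly throws away a quarter of its precision. The document does not support that. Baseline is already in the GEE as a repeated measure, and a change contrast does account for baseline differences, only less efficiently. The mean model is not written out, which a journal article may leave to the full plan. The present wording is compatible with a common baseline mean, and under that model the loss is zero. The 25% also belongs to one visit at one planning value of ρ, applied alike to the 1-day, 40-day and 1-year measurements.

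All of this stands, and it makes the loss conditional. It does not remove the point, because the point does not rest on silence: Table 1 lists the covariates for both GEE and ANCOVA and states a change-from-baseline contrast, and nothing there secures the efficient version.

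A reader might also infer bias or a known loss of power. Neither follows. Under randomisation the unadjusted and change-score contrasts are valid with robust standard errors, and without a K10 standard deviation no power can be computed.

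Finally, participants draw the envelope holding their assignment at consent, before the baseline session. Both forms of adjustment work most cleanly if knowledge of the group has not moved the baseline score. The timing of that measurement is a separate, procedural question.

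**Conclusion.** The point holds as one of efficiency and specification. As written, the between-group analyses do not secure the gain from baseline K10. If group means at baseline are left free, adjustment would cut the variance of a single-visit contrast by 25% at the plan's ρ of 0.5, and by 15% to 35% against change scores across ρ from 0.7 down to 0.3. Against follow-up-only comparisons the range is 9% to 49% as ρ rises from 0.3 to 0.7. If a common baseline mean is what the authors intend, nothing is lost and the plan need only say so.

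The figures assume equal variances at each visit, exchangeable correlation, complete data, and a baseline score not shifted by knowledge of the allocation. The change should be made because it costs little, but the trial's validity does not depend on it.

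**What to change.** Under Primary analysis, state how baseline K10 enters the between-group model, in one of two ways:

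1. Keep all four time points in the GEE, with group, time and group-by-time terms, and constrain the group means to be equal at baseline. This also serves the planned within-group comparisons over time.
2. Model the three follow-up K10 scores with group, time, group-by-time and baseline K10 as a covariate. Baseline is then no longer an outcome, so a separate model must be kept for the within-group comparisons with the pre-intervention score, on which Table 1 question 1 depends.

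In either case, report the group difference at each follow-up and add baseline K10 to the ANCOVA covariates, including in Table 1.

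The cost is a sentence or two in the analysis section and a matching edit to Table 1. It needs no new data and no extra participants. The article already provides for updating its analysis plan; the choice should be fixed before the interim analysis in Weeks 13–19. When baseline is measured relative to the envelope draw is not part of this change.
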